### 5.2.2 COVARIATE ADJUSTMENT

Not applicable.

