### 1.2 OBJECTIVES

To determine whether, at an NHS Trust level, having a suspected COVID-19 assessment pathway which incorporated PCT testing, modified the impact of the first COVID-19 wave on antibiotic use (both on a predefined set of antibiotics used for community-acquired pneumonia (CAP) and total antibiotics).

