### 3.3 ANALYSIS POPULATION

To reduce the risk of bias, we will use data from all acute and teaching NHS hospital Trusts (i.e. excluding specialist hospitals) in England and Wales caring for COVID-19 inpatients over 16 years of age between 24 February 2020 and 05 July 2020. Routine hospital activity has markedly reduced during COVID-19 (e.g. cancellation of elective work) and this will have affected antibiotic prescribing and makes the pre-COVID-19 prescribing data invalid for comparison. In addition, PCT testing is expected to impact primarily on suspected COVID-19 patients who will only make up a proportion of inpatients at any one time. Hospital activity data will therefore be used to control for reduced inpatient activity.

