## 5. ANALYSIS

### 5.1 OUTCOME DEFINITIONS

#### 5.1.1 PRIMARY OUTCOME(S)

Weekly trend of:

- number of defined daily doses (DDDs) of all antibiotics excluding anti-TB drugs, etc. (total DDDs, ‘tDDD’) per total number of admissions

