## 5.2 ANALYSIS METHODS

### 5.2.1 LIST OF METHODS AND PRESENTATION

A controlled interrupted time series (ITS) will be undertaken with variable dates of introduction of PCT testing across Trusts (McLintock et al. 2014; Kontopantelis et al. 2015; Bernal et al. 2017, 2018; Bottomley et al. 2019; Bell et al. 2021).

We will fit a linear mixed effects model with ISO week, use of PCT testing (yes/no) in ICU in each ISO week, use of PCT testing (yes/no) in ED/acute wards in each ISO week, and their interaction with ISO week as independent fixed-effect variables, and Trust as a random-effect variable. Based on this ‘segmented’ regression model, we will estimate the level and trend of the rate of antibiotic usage before and after the introduction of PCT testing and test the null hypotheses that 1) the level (i.e. model intercept) and 2) the trend (i.e. model slope) do not change following the introduction of PCT testing.

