### 5.2.5 SENSITIVITY ANALYSES

In addition to the 'step change' assumed for the Trusts introducing PCT testing (i.e. assuming an instant change in practice following the introduction) in the primary analysis we will also model a more gradual 'phase-in' e.g. over a four-week period.

We will consider adjusting for hospital occupancy (i.e. bed days divided by capacity) by including it as a covariate in the analysis model.

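### The primary model has no Trust-week measure of COVID-19 burden, so if PCT introduction dates follow local surges, surge timing can confound the PCT estimates

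*SAP*

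**What the plan says.** SAP 1.2 sets the objective at Trust level: whether a pathway with PCT testing "modified the impact of the first COVID-19 wave on antibiotic use".

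SAP 5.1.1 defines the primary outcome as the weekly trend in total DDDs "per total number of admissions". SAP 5.2.1 gives the model: "We will fit a linear mixed effects model with ISO week, use of PCT testing (yes/no) in ICU in each ISO week", the same for ED/acute wards, and "their interaction with ISO week as independent fixed-effect variables, and Trust as a random-effect variable". Under "COVARIATE ADJUSTMENT", section 5.2.2 reads "Not applicable".

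SAP 3.3 recognises that "PCT testing is expected to impact primarily on suspected COVID-19 patients who will only make up a proportion of inpatients at any one time". Its stated response is to use activity data to control for lower inpatient activity.

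The only covariate named anywhere is in 5.2.5, as an optional sensitivity analysis: "We will consider adjusting for hospital occupancy (i.e. bed days divided by capacity").

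Weekly activity data are obtained (5.1.2). Four of the seven secondary outcomes in 5.1.3 are weekly rates per COVID-positive admission or bed day, so weekly COVID-positive counts must be in the dataset.

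**The concern.** A rate per admission removes the effect of having fewer patients. It does not remove the effect of having different patients. As a Trust's surge builds and fades, the proportion of its admissions with COVID-19 changes, and DDDs per admission can change with it even if prescribing for each type of patient stays the same.

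The window, ISO weeks 9 to 27, was chosen to span the first peak (2.7), so every adopter starts or extends PCT inside the wave. If Trusts did so in response to their own surge, the before/after contrast within adopters partly compares different stages of that surge. Never-users and always-users show the common calendar pattern, not each adopter's own. The level and trend tests in 5.2.1 could then reject, or miss an effect, for reasons unrelated to PCT.

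The objective also concerns the wave's impact, and the model represents the wave only through calendar week.

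**Working it through.** The SAP states no power, effect size or variance, so there is no figure of its own to reproduce. What follows sets out the mechanism and then two illustrations whose inputs, other than the series size, are assumptions.

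**1. Mechanism.** Let s be the COVID-positive share of admissions, n the DDDs per other admission and d the extra DDDs per COVID-positive admission. Then DDDs per admission = n + s·d. If s moves from 2% to 30% (assumed values), the outcome moves by (0.30 − 0.02)·d = 0.28·d with no change in prescribing to either group. Total admissions cancel, so the denominator does not correct this.

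**2. Simulation of the mixed model, true PCT effect zero.** From the SAP: 19 weeks and 110 Trusts (midpoint of the 100–120 in 2.3). Assumed: 40% adopters, 30% never-users, 30% always-users; one PCT indicator for simplicity; bell-shaped local wave (SD 2.5 weeks); local peaks varying with SD 1.5 weeks; wave adding 0.5 or 1.0 DDD per admission at an average peak; Trust SD and residual SD both 0.5; 60 runs per scenario. Level is read at mid-window. Paired figures are for wave effects 0.5 / 1.0.

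Adoption about two weeks before the local peak:

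| Time and covariate terms | Level bias | Level false positives | Slope bias per week | Slope false positives |
|---|---|---|---|---|
| Linear week (5.2.1) | 0.18 / 0.34 | 98% / 100% | −0.011 / −0.022 | 60% / 95% |
| Quadratic week (5.2.4) | 0.11 / 0.20 | 55% / 93% | −0.006 / −0.012 | 27% / 55% |
| Full week effects | 0.07 / 0.13 | 23% / 62% | −0.002 / −0.004 | 7% / 22% |
| Linear week + COVID covariate | 0.015 / 0.015 | 7% / 2% | 0.000 / 0.000 | 5% / 8% |

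Adoption unrelated to the local peak:

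- Linear week: level bias about −0.02, false positives 5% / 5%; slope bias −0.009 / −0.017, false positives 47% / 87%.
- Quadratic week: slope false positives 8% / 7%.
- Linear week + COVID covariate: slope false positives 3% / 2%.

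With 60 runs, the standard error of a true 5% rate is √(0.05 × 0.95 / 60) = 2.8 percentage points, so rates of 2% to 8% are compatible with 5%. The covariate here was a nearly exact measure of the wave, so its performance is a best case.

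**3. Dependence on timing.** A closed-form calculation for 110 Trusts split 40/35/35 across the exposure groups, peak SD 2 weeks, wave SD 3 weeks, wave height 1 (two residual SDs) and no PCT effect gives this spurious level change at introduction, as a fraction of wave height:

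| Start relative to local peak | Quadratic week | Week factor |
|---|---|---|
| Two weeks before | 0.27 | 0.20 |
| One week before | 0.18 | 0.14 |
| One week before, 3-week scatter | 0.07 | 0.06 |
| At the peak | 0.04 | 0.06 |
| Two weeks after | −0.17 | −0.10 |

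For an exact start one week before, z is about 3.5 and 2.7. At the peak it is 1.0 and 1.3, and with scatter 1.6 and 1.3. With peak SD 1 week, the one-week-before figures fall to 0.14 and 0.06. With timing unrelated to the peak and a week factor, the result is about 0.

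**The case against.** The strongest reply is that the SAP handles activity through its denominators by design (2.1, 3.3), so the entry in 5.2.2 is consistent with the plan, and that several other provisions bear on the wave. Each helps in part:

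- Never-users and always-users (4.5.2) are concurrent comparators, but for the shared calendar pattern only.
- Non-linear week terms (5.2.4) are conditional and give one curve for all Trusts. Trust-specific slopes are optional and linear, so they cannot follow a local rise and fall.
- Occupancy (5.2.5) is optional and measures how full a hospital is, not how much of its work is COVID-19.
- COVID-positive denominators (5.1.3, 5.2.6) divide all antibiotic use by a count that itself follows the wave. They define different outcomes and leave the primary one unadjusted.

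Two stronger readings are tempting. A reader might infer that surge timing does bias the PCT effect. The SAP does not support that: 5.2.1 says only that introduction dates vary, nothing links them to local surges, and section 3 of the working shows that size and even sign change with the assumed timing. A reader might also infer that the model cannot address the objective, or forces a constant PCT effect. That goes too far: the PCT by ISO week interactions let the effect change over a window chosen to span the peak. They do so linearly in calendar time, and a given week can be a different stage of the wave in different Trusts.

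Objections to the remedy also stand in part. COVID-positive share of admissions shares its denominator with the primary outcome, so noise in admissions induces correlation between them. Section 3.3 speaks of suspected patients, whereas the covariate counts positive ones.

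**Conclusion.** The point holds as a conditional one. The primary model has no Trust-week measure of COVID-19 burden, the data for one are already obtained, and no existing provision adjusts the primary outcome for Trust-specific surges. If introduction dates are related to a Trust's own surge, the level and trend estimates can be confounded, and shared time terms, even a full week factor, do not fully remove this.

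The level bias needs that relation, which is plausible because adoption falls inside the wave but is not shown. The trend estimate was biased in the simulation even without it while week stayed linear; quadratic week largely cured that. All magnitudes rest on assumed wave height, peak spread and timing, so only the mechanism should be relied on. Making PCT by COVID share the primary estimand would be arguable and is not required, least of all for Wales. This warrants an amendment to the primary model but does not invalidate the design.

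**What to change.** Replace the entry in 5.2.2 with wording such as:

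> *The primary model will include, as a fixed effect, the COVID-positive share of activity in each Trust and ISO week (zero where there are none), together with flexible calendar-time terms. The model without this covariate will be reported as a sensitivity analysis.*

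State whether the share is of admissions or of bed days. For the admissions-based primary outcome, the bed-day share avoids a common denominator.

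Add PCT by COVID share, for both PCT indicators, as a prespecified supporting analysis that addresses objective 1.2 directly, mainly for England.

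Cost: SAP wording and a few parameters. England offers up to 100 × 19 = 1,900 to 120 × 19 = 2,280 Trust-weeks. The separate Welsh analysis has at most 15 × 19 = 285 to 20 × 19 = 380 hospital-weeks, so it will lose precision. Some confounding will remain because positive counts under-ascertain suspected COVID-19, particularly if ascertainment varied by Trust or week. The report should say so.

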### 5.2.3 ASSUMPTION CHECKING

We will check for autocorrelation by checking plots of residuals and (partial) autocorrelation functions and by performing Durbin-Watson tests.

Additionally, we will perform standard regression diagnostics (e.g. residuals vs. fitted plots) to assess basic assumptions such as linearity, normality, and homoscedasticity, as well as inspecting outliers.

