## 2.3 SAMPLE SIZE

Specifying a formal sample size target is not possible as this is an opportunistic retrospective analysis of antibiotic prescription data provided by our partners Rx Info Ltd, Public Health England (PHE) and Public Health Wales (PHW). Data will be available for around 100-120 English NHS Trusts and around 15-20 Welsh NHS hospitals, with up to 19 weekly data points for each.

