# 3. STATISTICAL PRINCIPLES

## 3.1 LEVELS OF CONFIDENCE AND P-VALUES

All hypothesis tests and confidence intervals (CIs) will be two-sided. We will use a 5% significance level and present 95% CIs.

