#### 5.1.2 TIMING, UNITS AND DERIVATION OF PRIMARY

Aggregated weekly antibiotic usage data (total dispensing to hospital locations) will be collected from Rx Info Ltd (and provided via PHE and PHW), and weekly patient activity data will come directly from PHE and PHW. As a consequence of the extraction and aggregation methods differing between PHE and PHW (as described in separate documents), English and Welsh data will be analysed separately.

Date of introduction of PCT testing, or not, and whether a Trust that did not introduce PCT testing between March and June 2020 was using it already or not, will be collected via direct contact with hospitals in WP 1.1. For the Trusts introducing PCT testing, their first week of PCT use will be defined as the ISO week following the reported introduction date.

The three different data elements (antibiotic usage, patient activity, PCT usage) will be merged to create a single analysis dataset; this will be done by matching their NHS Organisational Data Service (ODS) codes.

tDDDs are defined as all ATC J01, J04AB02 (rifampicin), A07AA12 (fidaxomicin) and A07AA09 (vancomycin – oral).

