### 5.2.4 ALTERNATIVE METHODS IF DISTRIBUTIONAL ASSUMPTIONS NOT MET

If the data show signs of autoregression, we will add a first-order autocorrelation and/or moving average covariance structure to the model.

If the trend over time in the data is distinctly non-linear, we will add additional terms (e.g. quadratic ISO week) to the regression model.

If appropriate, we will consider more complex random effects such as Trust-specific slopes in addition to Trust-specific intercepts.

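### Durbin-Watson, the only formal autocorrelation test in SAP 5.2.3, is built for one OLS series, and its use on a multi-Trust mixed model is unspecified, so weak autocorrelation (weak to moderate in Wales) can be missed

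*SAP*

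**What the plan says.** SAP section 5.2.1 sets one mixed model over all Trusts: "We will fit a linear mixed effects model with ISO week, use of PCT testing (yes/no) in ICU in each ISO week", with further PCT and interaction terms, "and Trust as a random-effect variable". Section 2.3 gives the size of the data: "Data will be available for around 100-120 English NHS Trusts and around 15-20 Welsh NHS hospitals, with up to 19 weekly data points for each". Section 5.1.2 adds that "English and Welsh data will be analysed separately", so there are two fits of very different size.

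For autocorrelation, section 5.2.3 says: "We will check for autocorrelation by checking plots of residuals and (partial) autocorrelation functions and by performing Durbin-Watson tests". Section 5.2.4 makes the model depend on the outcome: "If the data show signs of autoregression, we will add a first-order autocorrelation and/or moving average covariance structure to the model". Section 3.1 sets the error rate: "All hypothesis tests and confidence intervals (CIs) will be two-sided. We will use a 5% significance level and present 95% CIs".

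The SAP does not say whether the test uses marginal residuals (Trust effect still in) or conditional residuals (Trust effect removed), how rows are ordered, or whether it is run once on all Trusts or once per Trust. Nor does it say which check prevails if they disagree.

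**The concern.** Durbin-Watson compares successive residuals of one ordered series from ordinary least squares. Here the residuals come from a mixed model and form many short series. Three things can go wrong:

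- In a stacked file, some successive pairs join the last week of one Trust to the first week of the next.
- Marginal residuals share the Trust effect, which looks like strong positive autocorrelation.
- A test per Trust has only 19 points.

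The result helps decide the residual covariance of the primary model, and so the standard errors of the level-change and trend-change tests. If positive autocorrelation is left out, those tests reject too often.

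**Working it through.** The SAP gives no figure for this check, so there is nothing of its own to reproduce.

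**Inputs from the SAP.** 110 English Trusts (midpoint of 100-120), 18 Welsh hospitals (within 15-20), 19 weeks, two-sided 5%. **Assumptions, not in the SAP.** Random intercept per Trust; intraclass correlation (ICC) 0.5, with 0.2 and 0.8 as the range for England; lag-1 correlation 0 to 0.5 within Trust; roughly a quarter to a third of Trusts in each of the adopter and always-user groups; one PCT indicator in place of two.

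**1. Stacking.** DW = Σ(r_t − r_(t−1))² / Σ r_t². England has 110 × 19 = 2090 rows and 2089 successive pairs. Of these, 109 cross a Trust boundary: 109/2089 = 5.2%.

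**2. Conditional residuals in Trust order, no autocorrelation.** Per Trust and in units of the residual variance:
- 18 within-Trust pairs give 18 × 2 = 36.
- The sum of squares is 19 × (18/19) = 18, so these pairs contribute 36/18 = 2.0.
- The boundary pair contributes 2 × (18/19)/18 = 0.105.

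The expected value is about 2.105; simulation gives about 2.10. The usual null SD is 2/√2090 = 0.044, so the shift is 0.105/0.044 = 2.4 SDs. In simulation the two-sided test signals in about 63% of England-sized data sets at ICC 0.5 (51-64% over ICC 0.2-0.8), always towards negative autocorrelation.

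**3. Marginal residuals, no autocorrelation.** Expected DW ≈ 2(1 − ICC)(18/19) + 2/19.

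| ICC | Formula | Simulated |
|---|---|---|
| 0.2 | 1.516 + 0.105 = 1.62 | 1.63 |
| 0.5 | 0.947 + 0.105 = 1.05 | 1.06 |
| 0.8 | 0.379 + 0.105 = 0.48 | 0.49 |

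The test rejects in 100% of runs because it picks up the Trust effect.

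**4. Detection with conditional residuals in Trust order (two-sided, ICC 0.5).** The upward shift hides weak positive autocorrelation.
- England: the lower limit is 2 − 1.96 × 0.044 = 1.91. At lag-1 correlation 0.1 the mean statistic is 1.93 and detection about 40% (35-48% over the ICC range). At 0.2 the mean is 1.75 and detection 100%.
- Wales: 18 × 19 = 342 rows, SD 2/√342 = 0.108, lower limit 1.79. Detection is about 9% at 0.1 and 60% at 0.2.

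**5. Conditional residuals sorted by week.** The statistic stays near 2.00, and even at 0.5 the test rejects in only 9-13% of runs.

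**6. One test per Trust (19 points).** Two-sided power is 11%, 19% and 42% at 0.2, 0.3 and 0.5. With 110 tests and no autocorrelation, 110 × 0.05 = 5.5 rejections are expected, and the chance of at least one is 1 − 0.95^110 = 99.6%.

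**7. Error rates if autocorrelation is left out (level / trend test, nominal 5%).**

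| Lag-1 correlation | England | Wales |
|---|---|---|
| 0.1 | about 8% / 8% | 6.8% / 6.7% |
| 0.2 | about 9% / 11% | 10.2% / 10.5% |

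Across runs, the Welsh figures lie at about 7-12%.

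**8. Weighting by the chance of a miss.** This takes 5% once AR(1) is fitted and treats detection as independent of the PCT test.
- England, 0.1: 0.60 × 8 + 0.40 × 5 = 6.8%. England, 0.2: about 5%.
- Wales, level test, 0.1: 0.91 × 6.8 + 0.09 × 5 = 6.6%. Wales, 0.2: 0.40 × 10.2 + 0.60 × 5 = 7.1%.

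**9. The alternative.** A likelihood-ratio test of AR(1) within Trust detected 0.1 in 99% of England-sized data sets. For Wales it detected 0.1 in 39% and 0.2 in 92%. By the same weighting, the Welsh level test then runs at 0.61 × 6.8 + 0.39 × 5 = 6.1% and 0.08 × 10.2 + 0.92 × 5 = 5.4%.

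**The case against.** **Stacking is inferred.** The SAP does not say that residuals are stacked, and the plural for the tests could mean one per Trust, which keeps the single-series form. This stands: the defect is a test that does not fit the model and is left open, not a stated misuse.

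**Durbin-Watson does not decide alone.** Residual plots and autocorrelation functions also feed the trigger in 5.2.4. This stands and limits the harm, although the SAP does not say that these functions are computed within Trust. The detection rates above treat the test as the sole trigger.

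**Per-Trust tests read together are not weak in England.** At 0.2, 110 × 0.11 = 12.1 rejections are expected against 5.5, with SD √(110 × 0.05 × 0.95) = 2.29, a gap of 2.9 SDs. This stands for England. For 18 Welsh hospitals it is 2.0 against 0.9, about 1.2 SDs, and the SAP gives no rule for combining the tests.

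**A false signal costs little.** It adds a parameter that should be estimated near zero. This stands.

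**A stronger reading to resist.** A reader might infer that the primary tests will run at 7-10% or more. The documents do not support that. With conditional residuals in Trust order, 0.2 is always detected in England, so the inflated rate there applies only to correlation near 0.1, and only if the plots miss it too.

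**Conclusion.** The point holds as a technical refinement of minor weight. The only formal test named does not fit the model, and its answer runs from about 1.06 to about 2.10 on data with no autocorrelation, depending on a choice of residuals that the SAP leaves open.

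The practical risk is a miss. In England it concerns autocorrelation near 0.1, with level and trend tests at about 8% if missed. In Wales it reaches about 0.2, with about 7-12% if missed. Week-sorted rows would be worse, but nothing in the SAP says that they will be used.

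The sizes rest on the assumed ICC, lag-1 correlations and PCT group split. The mismatch between test and model does not.

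**What to change.** In section 5.2.3, replace the Durbin-Watson tests with wording such as:

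> Once the time trend and the random effects are settled, residual autocorrelation is assessed by a REML likelihood-ratio (or AIC) comparison of the nlme model with and without an AR(1) structure indexed by ISO week within Trust, and with a moving-average term where the autocorrelation function suggests one. Autocorrelation and partial autocorrelation functions are computed within Trust from normalised residuals.

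Choose likelihood ratio or AIC in advance, and name that result as the trigger in section 5.2.4. The order matters because omitted Trust-specific slopes can pass for autocorrelation. With no autocorrelation and a slope SD of 0.05 in the simulation's units, one-sided positive signals from the stacked test rose from 0% to 18%.

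The cost is SAP wording and one or two extra fits in a package that section 5.6 already names. The moving-average option of 5.2.4 is kept. The procedure remains a pre-test with limited power for weak autocorrelation in the Welsh data (39% at 0.1). Fitting AR(1) within Trust from the start would avoid that, at the price of one more parameter.

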### 5.2.4 ALTERNATIVE METHODS IF DISTRIBUTIONAL ASSUMPTIONS NOT MET

If the data show signs of autoregression, we will add a first-order autocorrelation and/or moving average covariance structure to the model.

If the trend over time in the data is distinctly non-linear, we will add additional terms (e.g. quadratic ISO week) to the regression model.

If appropriate, we will consider more complex random effects such as Trust-specific slopes in addition to Trust-specific intercepts.

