## 2.7 TIMING OF OUTCOME ASSESSMENT

We will use aggregated data from acute admissions to Trusts between ISO weeks 9-27 (24 February 2020 to 05 July 2020 inclusive) to encompass the first peak of the COVID-19 pandemic across the UK.

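### A curved time trend was foreseeable in a window chosen to contain the epidemic peak, yet the primary model takes ISO week as linear and adds curvature only on an undefined trigger, so part of the wave can be attributed to PCT

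*SAP*

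**What the plan says.** Section 2.7 sets the window at ISO weeks 9–27, "to encompass the first peak of the COVID-19 pandemic across the UK". Section 1.2 asks whether PCT testing modified the effect of that wave on antibiotic use, so the plan itself presumes that the wave matters.

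Section 5.2.1 gives the primary model: "We will fit a linear mixed effects model with ISO week, use of PCT testing (yes/no) in ICU in each ISO week", a matching indicator for ED/acute wards, the interactions of both with ISO week, and a random effect for Trust. The second of the two null hypotheses concerns "the trend (i.e. model slope) do not change following the introduction of PCT testing". Time is therefore read as a slope, and PCT as a change in intercept and slope. Section 5.2.4 confirms this, since it treats a quadratic as something extra: "If the trend over time in the data is distinctly non-linear, we will add additional terms (e.g. quadratic ISO week) to the regression model".

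The trigger is section 5.2.3, which promises "standard regression diagnostics (e.g. residuals vs. fitted plots) to assess basic assumptions such as linearity, normality, and homoscedasticity". Section 5.2.2 plans no covariate adjustment. Section 5.2.5 offers only this, as a sensitivity analysis: "We will consider adjusting for hospital occupancy (i.e. bed days divided by capacity) by including it as a covariate in the analysis model".

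The data are expected to cover "around 100-120 English NHS Trusts and around 15-20 Welsh NHS hospitals, with up to 19 weekly data points for each" (2.3), with England and Wales modelled separately (5.1.2).

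**The concern.** A straight line cannot follow a rise and fall. The design is a controlled interrupted time series, and the value of the control Trusts is that they show what happened in the same calendar weeks without a change in PCT use. That value is partly lost if the common time pattern is forced into a shape it does not have. Never-users, always-users and adopters all share the mis-shaped term. Adopters, however, change PCT state during the wave, so the PCT indicator and its interaction with week can absorb what the line leaves over.

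Both primary null hypotheses are affected, and the secondary outcomes in 5.1.3 use the same model. The repair in 5.2.4 depends on a judgement made after seeing the data, with no threshold and no fixed final form.

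**Working it through.** **The plan's own figure.** 24 February 2020 is day 1 of ISO week 9 and 5 July 2020 is day 7 of ISO week 27, so there are 27 − 9 + 1 = 19 weekly points, as 2.3 states. Trust-weeks are 100 × 19 = 1,900 to 120 × 19 = 2,280 in England and 15 × 19 = 285 to 20 × 19 = 380 in Wales. The SAP gives no rate, SD or wave size, so everything below rests on stated assumptions.

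**Model simulated, with a true PCT effect of zero.**

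y(i,t) = Trust effect(i) + f(t) + β₁·PCT(i,t) + β₂·PCT(i,t)·(t − c) + error, with β₁ = β₂ = 0.

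f(t) was fitted as a line, as a quadratic, or as one effect per week. One PCT indicator was used, where the SAP has two.

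**Set A: joint 2-df test of β₁ and β₂ at 5%.** Assumed: 110 Trusts (40 never-users, 30 always-users, 40 adopters), residual SD 0.5, a common bump peaking at week 15, and introduction windows from weeks 11–14 to weeks 10–26.

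| Bump height | Linear week | Quadratic week | Week as factor |
|---|---|---|---|
| 1.0 | 86–100% | 6–96% | 2–5% |
| 0.3 | 16–86% | 7–21% | 2–7% |

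For the quadratic, the spread comes mainly from the introduction window. A separate run of 150 datasets per cell (Monte Carlo SE at 5%: √(0.05 × 0.95/150) ≈ 1.8 points) gave these joint rejection rates:

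| Introduction weeks | Bump 1.0 | Bump 0.3 |
|---|---|---|
| 11–14 | 98% | 23% |
| 12–16 | 53% | 7% |
| 14–18 | 60% | 11% |
| 12–22 | 23% | 7% |
| 10–26 | 9% | 7% |

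With a bump of 1.0, the spurious effect at week 15 reached +0.50 (linear) and +0.23 (quadratic), that is, half and about a quarter of the wave height. With introduction in weeks 14–18 it was +0.07 under the line and −0.10 under the quadratic.

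**Set B: level and slope tested separately, as in 5.2.1.** Assumed: baseline rate 1, between-Trust SD 0.20, residual SD 0.15, the same 110 Trusts, introduction in weeks 11–16, a skewed wave peaking at week 15, week centred at 18, and 200 datasets per cell. The wave-to-noise ratios are close to Set A: 0.10/0.15 = 0.67 and 0.30/0.15 = 2, against 0.3/0.5 = 0.6 and 1.0/0.5 = 2.

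| Wave | Time term | False level change | As share of wave | Level rejections | Slope rejections |
|---|---|---|---|---|---|
| 0.10 | linear | +0.0315 | 0.0315/0.10 = 0.32 | 61% | 45% |
| 0.10 | quadratic | +0.0047 | 0.0047/0.10 = 0.05 | 7% | 8.5% |
| 0.10 | factor | −0.0017 | about 0 | 5.5% | 5.5% |
| 0.30 | linear | +0.0967 | 0.0967/0.30 = 0.32 | 100% | 99.5% |
| 0.30 | quadratic | +0.0177 | 0.0177/0.30 = 0.06 | 20.5% | 28% |
| 0.30 | factor | −0.0017 | about 0 | 5.5% | 5.5% |

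The reason is visible in the fit to the wave alone. A line explains 16% of its variance over weeks 9–27 (0% for a symmetric wave peaking at week 18), and a quadratic explains 73% (91%).

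**Wales.** With 17 hospitals (6 never-users, 4 always-users, 7 adopters), introduction in weeks 11–16 or 12–22 and either wave shape, level rejections were 3–80% with linear week. Quadratic week gave 3–9% and the factor 3–10%. At this size the gain over the line is clear, but there is none to see over a triggered quadratic.

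**Limit of week effects.** Suppose each Trust has its own peak (SD 1.5 weeks) and adopters start between two weeks before and one week after it. With a wave of 0.30, the factor then leaves a false level change of +0.022 and 39% level rejections, close to the quadratic (+0.026, 38.5%). The line gives +0.083 and 100%.

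**The case against.** The strongest reply is that the plan already provides the remedy. Section 5.2.3 checks linearity. Section 5.2.4 commits to adding terms once curvature is seen, and the quadratic is only its example, so splines, higher powers or week effects all fall within it. With a bump of 1.0, the quadratic term was significant in every simulated dataset, so the straight line would hardly survive the checks. A quartic brought joint rejection down to 3–19% for clustered introduction and 1–6% for wide windows. This stands in part. The linear figures describe the model as specified, not necessarily the one finally reported, and it would be wrong to say that the SAP allows nothing beyond a parabola. What remains is that neither trigger nor final form is fixed, and that the one form named can still fail badly.

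It also stands that the sizes depend on unknowns. Section 4.5.2 lets adopters start or extend PCT use at any time in weeks 9–27, and with wide spread the quadratic is near nominal. The outcome is a rate per admission, so the wave in that rate could be small.

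Three stronger readings are tempting and are not supported:
- **A reader might infer that the whole rise and fall of the wave is credited to PCT.** The simulations show a part: about a third of its height as a level change (Set B, linear) and at most about half at week 15.
- **A reader might infer that the sign of the bias follows only from whether Trusts adopted before or after the peak.** The weeks 14–18 case reverses sign between the linear and quadratic fits with the same timing.
- **A reader might infer that week effects cure the problem.** They do so only for the time pattern that all Trusts share.

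**Conclusion.** The concern holds in limited form. A curved trend could be foreseen from 1.2 and 2.7, yet the primary time term is linear and its correction is left to an undefined judgement. When introduction clusters around the peak, the controls do not prevent part of the wave from entering the PCT level and slope terms.

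Under the assumptions above, false rejection on the joint test is about 16–100% with linear week and 6–96% with quadratic week. The quadratic is worst for a large bump with clustered introduction and near nominal for the widest window. Week as a factor gives 2–7% when the wave is common to all Trusts. These ranges rest on assumed wave sizes, SDs, Trust splits and introduction dates, and on a single PCT indicator. They show that the mechanism works and how far it can reach; they do not predict the bias in the actual data.

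This should be fixed before analysis. It is not rated higher because 5.2.4 already commits to extra terms once curvature is recognised, and these can remove much of the bias.

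**What to change.** - **Section 5.2.1:** enter ISO week as a 19-level factor shared by all Trusts within each country's model. Keep linear week only inside the two PCT-by-week interactions. The trend term then measures divergence from Trusts in the other PCT state in the same weeks.
- **Section 5.2.4:** delete the conditional rule on non-linear trend.
- **Section 5.2.5:** add a sensitivity analysis with region-by-week effects, or with a weekly Trust-level COVID-19 activity term, in case introduction followed local peaks. COVID-positive admissions and bed days are already collected (4.5.1, 5.1.3).

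**Cost.** The change is to SAP wording only, with no new data for the activity-term option. The factor uses 18 parameters where the line uses 1, so 17 extra, against 1,900–2,280 English or 285–380 Welsh Trust-weeks. Precision falls somewhat in the small Welsh dataset. There is no longer a single underlying weekly slope to quote; report the fitted weekly means instead.
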